Our proposed project, Decision Aid to Technologically Enhance Shared decision making (DATES), will test CW’s effectiveness for increasing CRCS and its facilitation of SDM in primary care practices through rigorous analysis of a conceptual model adapted from the Theory of Planned Behavior [49-53] (See Figure 1). It provides a framework that clarifies the relationship between DAs and SDM [54,55]. The theory incorporates three patient determinants (attitude, subjective norm and perceived self-efficacy) that influence patient intention, which in turn influences patient behavior. In our conceptual model, we have added knowledge to patient determinants, since DAs increase knowledge [56,57]. Additionally, based on our pilot randomized controlled trial, we believe that the patient’s preference toward a specific CRCS test option is a key mediator between CW and patient intention to undergo screening for CRC. Thus, interaction with CW positively affects patient determinants, leading to the patient establishing a preference for a particular CRCS test option. This leads to greater patient intention to undergo screening and ultimately, higher CRCS rate. This process is also mediated by what occurs between the patient and the clinician during the clinic visit to discuss CRCS: the degree of SDM reached and whether the patient and the clinician agree on which CRCS test option to choose. The latter will be termed concordance.

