### Aim 1: to measure the impact of CW on patient uptake of CRCS

H-1: patients in the intervention arm will have higher rates of CRCS adherence at the six month follow-up than those in the control arm.

The study arms will be compared to assure that randomization achieved similar study population with respect to age, gender, race, previous CRCS, practice site, and data completion. Medically documented completion of CRCS will be compared between the intervention arm and the control arm by means of a chi-square test (unadjusted analysis) and a logistic regression adjusting for potential predictors at baseline. The regression analysis will be performed with data at the patient level with completing CRCS (yes/no) as the outcome measure and the arm assignment (intervention arm versus control arm) as the main covariate of interest. The practice indicator will further be included as a covariate in order to account for the variation between practices. The clustering effect due to clinician will be accounted for by using a generalized estimating equations approach. Personal patient-level background information (for example, age, race, education, marital status, smoking, health status, health insurance) from the patient baseline survey will be considered for inclusion in the regression model. The model will further be adjusted for information about the patient’s past experience with the CRCS procedures and the baseline level of patient determinants (for example, knowledge, attitude, subjective norm, self-efficacy) and intent. We will also adjust for OPTION score and pertinent clinician-level covariates such as the clinician’s communication style from the clinician survey. In order to understand whether there is any difference in the completion of CRCS rates between groups of patients who (a) complete the risk assessment tool only, (b) complete the preference clarification tool only, (c) complete both, and (d) complete neither, we will use a four level factor indicating this group membership as an independent variable in the regression model.

The contribution of a specific group of covariates will be measured by means of increase in generalized R-square defined as:$$R^{2}\left(\mathrm{increase}\right)=\exp\left(-L_{1}^{2}/n\right)-\exp\left(-L_{2}^{2}/n\right)$$where $L_{1}^{2},L_{2}^{2}$ are the likelihood ratio statistics of the smaller and larger models, respectively.

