Secondary analysis will be carried out by means of Structural Equation Modeling approach to estimate the parameters of the analysis model (Figure 4) that corresponds to the conceptual model (Figure 1) [49,58-61]. Specifically, a path analysis will estimate the direct and indirect effects in order to identify the significance or otherwise of specific causal relationships. These will be done by standard *t* or *F-*tests in the context of a multiple regression analysis. Testing mediation (indirect) effects will further require using Sobel’s formula [82]. Moderation is investigated by testing for significance of hypothesized interaction terms or interaction effects that are identified during the initial screening. The analysis model will have several variables: subjective norm, perceived self efficacy, patient preference, and patient intention, each measured longitudinally; concordance, measured at one time point; practice indicators, intervention arm versus control arm, clinician communication style, SDM, and patient behavior/action each measured once along with the covariates identified during the preliminary screening. Figure 4 illustrates the full complexity of the theorized causal pathway.

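### The secondary path analysis tests mediation with the conservative Sobel formula, omits knowledge and attitude from its written variable list, and fixes no scale for its yes/no variables

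*Protocol article*

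**What the plan says.** The paragraph on Structural Equation Modeling under Analysis, Aim 3, makes three choices.

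- **Tests.** Direct paths are judged by t or F "tests in the context of a multiple regression analysis". For indirect effects, "Testing mediation (indirect) effects will further require using Sobel’s formula".
- **Variables.** The listed variables are "subjective norm, perceived self efficacy, patient preference, and patient intention, each measured longitudinally", then concordance, practice, arm, clinician communication style, SDM, screening action and any covariates retained by screening. The paragraph says that this analysis model matches the conceptual model of Figure 1.
- **Power.** Sample size and power gives one figure for this analysis: above 99% for a test of the overall model, with 600 patients and more than 100 degrees of freedom.

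The Background describes the conceptual model differently: "The theory incorporates three patient determinants (attitude, subjective norm and perceived self-efficacy) that influence patient intention", and "In our conceptual model, we have added knowledge to patient determinants, since DAs increase knowledge".

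Under Aim 1, the contribution of a group of covariates is measured by an increase in generalized R-square, whose inputs "are the likelihood ratio statistics of the smaller and larger models, respectively". The same section handles clinician clustering by generalized estimating equations (GEE).

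**The concern.** The article presents its main contribution as an explanation of how the decision aid works, and this analysis is where direct and indirect effects are estimated. Four things could weaken it.

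1. Sobel's formula treats the product of two estimated coefficients as normal. When either path is weak the product is skewed, and the test rejects too rarely.
2. Two of the four patient determinants are absent from the written list. A determinant that is not in the model cannot be shown to mediate.
3. Screening, clear preference and concordance are yes/no variables, analysed by logistic regression in Aims 1 to 3. The path analysis uses t and F tests and names no link, estimator or effect scale for them.
4. The Aim 1 R-square needs a likelihood, and GEE does not have one.

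**Working it through.** **1. The plan's own figures.** For a difference of 0.23 SD with 300 per arm, the standard error is √(2/300) = 0.0816, z = 0.23/0.0816 = 2.82, and power is Φ(2.82 − 1.96) = 80%, as stated. For overall model fit the article gives no RMSEA values. I assumed 0.05 against 0.08 with 100 degrees of freedom and N = 600. The noncentralities are 599 × 100 × 0.05² = 149.75 and 599 × 100 × 0.08² = 383.36, and power exceeds 99.99%. The pairs 0.05 against 0.01 and 0 against 0.05 give the same. The stated figure reproduces, but it concerns overall fit and says nothing about any indirect effect.

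**2. Sobel's formula.** Let a be the arm-to-mediator path and b the mediator-outcome path, with z-values za and zb. Then

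z(Sobel) = ab/√(a²·sb² + b²·sa²) = za·zb/√(za² + zb²),

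which is always below the smaller of za and zb. Take a = 0.23, so za = 2.82. With unit residual SDs, sb ≈ 1/√600 = 0.0408. At b = 0.10, zb = 0.10/0.0408 = 2.45. Both paths are expected to pass 1.96, yet z(Sobel) = 2.82 × 2.45/√(2.82² + 2.45²) = 1.85 does not.

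Simulated power, N = 600, continuous mediator and outcome, independent patients (ranges cover separate runs):

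| a | b (assumed) | Sobel | Percentile interval for ab | Loss, points |
|---|---|---|---|---|
| 0.23 | 0.10 | 31–32% | 51–54% | 20–22 |
| 0.23 | 0.12 | 45% | 65% | 20 |
| 0.23 | 0.14 | 55% | 75% | 20 |
| 0.23 | 0.15 | 59–63% | 75–77% | 14–16 |
| 0.23 | 0.20 | 73–74% | 79–80% | 6 |
| 0.23 | 0.30 | 77–79% | 80–81% | 1–4 |
| 0.30 | 0.30 | 95% | 96% | 1 |

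A closed-form check at b = 0.10: both paths are significant with probability Φ(0.86) × Φ(0.49) = 0.804 × 0.688 = 55%. The simulation of that joint test gave 55%.

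Type I error with a = 0 and b = 0.30 was 3.4% for Sobel and 3.9% for the interval. With both paths null it was 0.0% and 0.2%. Another run with one null path gave 5.6% for the interval.

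**3. Scale for yes/no variables.** Assumptions: the mediator rises from 35% to 50% (15 points, the plan's own detectable difference for dichotomous outcomes), control screening is 24% (the plan's value), and the direct log-odds ratio is 0.4. The logistic arm-to-mediator path is logit(0.50) − logit(0.35) = 0.619.

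| Logistic b | Product 0.619 × b | True indirect log-odds ratio | Product ÷ total log-odds ratio | True share, risk difference |
|---|---|---|---|---|
| 0.5 | 0.31 | 0.075 | 0.31/0.471 = 66% | 0.0166/0.0958 = 17% |
| 1.0 | 0.62 | 0.150 | 0.619/0.530 = 117% | 0.0332/0.1092 = 30% |
| 1.5 | 0.93 | 0.220 | 0.929/0.577 = 161% | 0.049/0.120 = 41% |

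If all paths are fitted by ordinary linear regression instead, ab averages 0.0153 against a true risk difference of 0.0166 (b = 0.5), and 0.0311 against 0.0332 (b = 1.0).

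**4. Variable list against the model.**

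| Determinant | Background model | H2-1 | Table 2, baseline and post-web | Path-model list |
|---|---|---|---|---|
| Subjective norm | yes | yes | yes | yes |
| Self-efficacy | yes | yes | yes | yes |
| Attitude | yes | yes | yes | **no** |
| Knowledge | yes | yes | yes | **no** |

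**5. R-square.** The increase is exp(−L1²/n) − exp(−L2²/n), where L1² and L2² are likelihood ratio statistics. GEE solves estimating equations without a likelihood, so neither is defined for the clustered fit.

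**The case against.** The strongest reply is that most of this is a matter of degree or of missing figures.

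- *Power.* A reader might infer that the mediation analysis is underpowered in general. The documents do not support that. They give no mediator-outcome path size, and the loss nearly vanishes by a slope of 0.30. With a = 0.23 SD the arm path alone holds every method near 80%, which is not Sobel's doing. Sobel errs on the cautious side, so it does not make a positive finding unsafe. All of this stands.
- *Scale.* A reader might infer that the indirect effects are mis-scaled as planned. The article never says that logistic coefficients will be multiplied, and read literally as linear regression the product is close to the true risk difference. What remains is that the text does not fix the scale, while the same variables have logistic models elsewhere. An article may leave that detail to a fuller document.
- *Model.* A reader might infer that the stated conceptual model is not tested. Figures 1, 3 and 4 are not shown and may contain knowledge and attitude, so this cannot be confirmed. Both might also enter as screened covariates, but that screening looks for confounding and moderation, and a covariate is not a mediator. The conflict between the written list and the Background stands either way.
- *R-square.* This is a descriptive measure in Aim 1, outside the mediation analysis. It needs one clarifying sentence.
- *Clustering.* Table 1 gives 49 clinicians in 14 practices, 30 of them in three practices. The simulations assume independent patients, so the gains and error rates above have not been shown for a bootstrap by clinician.

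**Conclusion.** The concern holds in a limited form. Sobel's formula is a conservative choice for the indirect effects. At N = 600 and a = 0.23 SD it costs about 15 to 22 points of power for slopes of 0.10 to 0.15, about 6 at 0.20 and almost none at 0.30. These figures assume continuous variables, independent patients and path sizes that the documents do not give.

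The written list leaves out two of the four determinants named in the Background and in H2-1, so list and model must be reconciled. This is the firmest part, because it rests on the text alone. The t and F tests do not match the logistic models used for the same yes/no variables, and indirect effects would be badly mis-scaled only if logistic coefficients were multiplied.

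The analysis is secondary. The primary comparison of screening between arms does not depend on it. The change is still worth making, because this is the analysis meant to explain the mechanism.

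**What to change.** 1. Replace Sobel's formula with a percentile bootstrap or Monte Carlo interval for each indirect effect, allowing for clinician clustering. Check the behaviour of a clinician-level bootstrap with 49 unevenly spread clinicians before relying on it.
2. Include baseline and post-web knowledge and attitude in the path model as mediators, and reconcile the written list with the diagram.
3. State one scale for screening, preference and concordance: either a categorical estimator, or linear models reported as risk differences. Do not multiply logistic coefficients.
4. Compute the Aim 1 R-square increase from an ordinary maximum-likelihood logistic fit, and say so.

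The cost is some programming and computing time. No new data are needed.

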### Sample size and power

In aims 1, 2 and 3, we make comparisons between the intervention arm and the control arm. The effect size we wish to detect between the study arms is 15%. Based on published data [48], the estimated proportion of study participants in the control arm that will complete CRCS by six months post intervention is 10 to 15%. Based on the pilot randomized controlled trial, the proportion is slightly higher (approximately 24%). We take this higher value as the anticipated rate in the control arm after six months, since this gives more conservative (larger) sample size estimates. To detect with 90% power a 15% increase in the completion rate in the intervention arm to be significant, one needs to have 213 patients per study arm. The calculation is based on a two-sided continuity-corrected chi-square test of independent proportions with 5% type-I error rate. Since we target to recruit 300 patients in each study arm, with a rough balance across practice, race, and gender, we have good power to detect such differences in the gender subgroups as well. For example, assuming that we have 150 men in each study arm, we have 76% power to detect the effect size described herein. With 300 patients per arm, a standardized mean difference of 0.23 can be detected between the two arms for continuous outcomes with 80% power. For dichotomous outcomes such as concordance, a 15% difference between the two arms can be detected with a power of ≥ 80%, when the percentage of occurrence in the control arm ranges between 25% and 50%. Thus, we are adequately powered to detect small differences for all aims. For the Structural Equation Modeling analysis, we estimate that the conceptual model will have > 100 degrees of freedom. Assuming a sample of 600 patients, power will be > 99% for a test of the overall model. Power to reject the model will be assessed by root mean square error of approximation [83].

## Discussion

### Rationale for undergoing the trial

The results of our proposed randomized controlled trial will be among the first to examine the effect of a real-time preference assessment exercise on CRCS and mediators, and, in doing so, will shed light on the patient-clinician communication and SDM ‘black box’ that currently exists between the delivery of DAs to patients and the subsequent patient behavior (that is, CRCS adherence). Our conceptual model will elucidate not only the mechanism of how a DA influences patient behavior, but also how the DA affects the SDM between the patient and the clinician [58-61]. In addition, CW has several highly innovative features. First, CW is an interactive web-based DA rigorously developed through extensive formative research [46-48]. Second, CW assists patients in clarifying their own CRCS preferences *and* risk. To our knowledge, no previous tools have integrated interactive preference clarification and personal risk assessment to tailor CRCS recommendation, not just assessing them separately [36]. Third, CW offloads the time devoted to providing knowledge, preference clarification, and risk assessment from the clinic visit, permitting the patient and clinician to engage in SDM at a more advanced level. Fourth, it can be easily incorporated into routine clinical care.

### Randomization strategy

Randomizing at the patient level facilitates recruitment and makes the study more feasible to complete in the given timeframe. Also, patient level randomization helps in balancing across potential patient level confounders and increases statistical power to detect an intervention effect. Clinicians will be blinded to the randomization. We considered randomization at the level of the practice. Such a design would be necessary if there was a risk of contamination between the intervention arm and the control arm within a practice if randomization occurred at the patient level. This is not a concern in our proposed project for two reasons. First, patients in the intervention arm will not have access to SW, and patients in the control arm will not have access to CW. Second, clinicians will not have the resources (time, expertise, desire) to replicate the CW experience. The clinicians could give an information brochure that replicates the SW content, but this would only be additive at best to either CW in the intervention arm or SW in the control arm.

### Alternative strategies

We considered providing the DA intervention through a compact disc. However, this would add substantial cost to the development. Also, an Internet-based approach would be much more feasible for future dissemination. We also considered recruiting patients without health insurance but decided to focus our efforts on over-sampling African Americans, to test in the community practices our pilot randomized controlled trial finding that CW led to increased CRCS adherence in both Caucasians and African Americans. We decided to provide CW in English only for this study, so that we could prove its effectiveness first before expanding to other languages, such as Spanish, with their attendant costs. Finally, because our focus was on how CW affects SDM between the patient and the clinician in community practices, we needed patients who had a primary care clinician and did not recruit patients without a primary care clinician.

Since CW has interactive risk assessment and preference clarification, we considered a 2 × 2 design of interactive risk assessment (+/-) and preference clarification (+/-). We also considered a three-arm study of SW, CW with interactive preference clarification only, and CW with interactive risk assessment and preference clarification. We ultimately decided against these designs due to feasibility and cost concerns in a multi-site community practice setting and the input from the practice clinicians that CW without risk assessment had no clinical utility. We utilize manipulation-check questions to understand what particular features of CW in the intervention arm were instrumental in the differential outcomes.

Ideally, the CW would be available to patients to complete from home prior to an appointment, thereby not requiring them to come an hour before an appointment. The original proposed study design was to have patients complete the website exposure from home with telephone assistance if needed. Reviewers expressed concern that this design would lead to significantly different experiences for each patient. Some might do it weeks ahead of time leading to discussion with many others about the decision. Others would wait to the very last minute to do it. Also, without the research team verification, a person other than the intended participant may actually log in to the website. The reviewers felt it was critical that everyone have the same exposure. The research team made the change with concerns that this would impair recruitment of clinicians and patients. However, this has not been a barrier to date.

### Dissemination

The participating clinicians receive regular newsletters and Email updates about the study. Upon completion of the study and analysis of data for the primary hypothesis, the participating clinicians will receive a summary report and be invited to meet with the PI for discussion. The participating patients will receive a summary letter about the results. Updates about the findings will be posted in each participating clinical site.

The data including audiotapes will be open to other investigative teams for additional analysis by contacting the PI with a formal request. Contact information will be provided with all presentations and publications. The request form is available as Additional file 8. Each request will be reviewed by the research team and the Data and Safety Monitoring Committee for approval.

### Future directions

Once our aims are accomplished, we can use the barrier and facilitator information to move into dissemination of the intervention, and address the issues above. Different language versions of CW can be created and tested. For dissemination, CW needs to be modified to a deliverable product that can be used alone, integrated into other’s website or electronic medical record, or used with mobile devices. Also, since we will now have information on how CW affects patient-clinician communication, CW can be tested as a community-wide intervention with particular efforts to target the patients without health insurance and/or PC clinicians. The recorded patient-clinician encounter will be a rich source of data for further exploration focused on communication, SDM, and competing demands addressed in the clinic visit. We are particularly interested in further examining the characteristics of patients and clinicians whose preferred decision making style leans towards SDM. In addition, we will have data related to facilitators, barriers, and cost to implement CW in community-based primary care practices. We will be able to perform cost effective simulation of CW.

## Trial status

Patient recruitment started in May 2012 and will continue through the end of September 2014. As of 28 October 2013, the study has recruited 339 participants (target: 600).

## Abbreviations

CRC: Colorectal cancer; CRCS: Colorectal cancer screening; CW: ColoDATES Web; DA: Decision aid; DAs: Decision aids; DATES: Decision Aid to Technologically Enhance Shared decision making; PI: Principal investigator; SDM: Shared decision making; SW: Standard web.
